# Efficacy of low-intensity pulsed ultrasound for the treatment of viral pneumonia: study protocol for a randomized controlled trial

**DOI:** 10.1186/s13063-023-07382-1

**Published:** 2023-06-09

**Keywords:** Viral pneumonia, Ultrasonic therapy, Ultrasonic waves, LIPUS, Inflammation

## Abstract

**Background:**

Viral pneumonia has always been a problem faced by clinicians because of its insidious onset, strong infectivity, and lack of effective drugs. Patients with advanced age or underlying diseases may experience more severe symptoms and are prone to severe ventilation dysfunction. Reducing pulmonary inflammation and improving clinical symptoms is the focus of current treatment. Low-intensity pulsed ultrasound (LIPUS) can mitigate inflammation and inhibit edema formation. We aimed to investigate the efficacy of therapeutic LIPUS in improving lung inflammation in hospitalized patients with viral pneumonia.

**Methods:**

Sixty eligible participants with clinically confirmed viral pneumonia will be assigned to either (1) intervention group (LIPUS stimulus), (2) control group (null stimulus), or (3) self-control group (LIPUS stimulated areas versus non-stimulated areas). The primary outcome will be the difference in the extent of absorption and dissipation of lung inflammation on computed tomography. Secondary outcomes include changes in lung inflammation on ultrasonography images, pulmonary function, blood gas analysis, fingertip arterial oxygen saturation, serum inflammatory factor levels, the sputum excretion volume, time to the disappearance of pulmonary rales, pneumonia status score, and course of pneumonia. Adverse events will be recorded.

**Discussion:**

This study is the first clinical study of the efficacy of therapeutic LIPUS in the treatment of viral pneumonia. Given that the current clinical recovery mainly depends on the body’s self-limiting and conventional symptomatic treatment, LIPUS, as a new therapy method, might be a major advance in the treatment of viral pneumonia.

**Trial registration:**

ChiCTR2200059550 Chinese Clinical Trial Registry, May 3, 2022.

**Supplementary Information:**

The online version contains supplementary material available at 10.1186/s13063-023-07382-1.

## Introduction

### Background and rationale {6a}

Viral pneumonia is a disease in which viral infection of the upper respiratory tract spreads downward, causing pulmonary inflammation and gas exchange abnormality, which is characterized by insidious onset and strong infectivity [1]. Most of the virus infections are mild to moderate and the clinical manifestations are mainly fever, headache, dry cough, and generalized myalgia. Other viruses can infiltrate the lungs and cause viral pneumonia. In recent years, some newly discovered cases of severe pneumonia caused by viruses have attracted more and more global attention, such as highly pathogenic avian influenza, adenovirus pneumonia, and novel coronavirus pneumonia, which are more serious among the elderly, obese, and patients with underlying diseases.

The treatment of viral pneumonia has always been a problem for clinicians. Due to the high variability of most viruses, the development of antiviral drugs faces great challenges. At present, symptomatic support treatment is the mainstay of clinical management.

Low-intensity pulsed ultrasound (LIPUS), a therapeutic ultrasound technique that has emerged in recent years [2], has been used to treat soft tissue and musculoskeletal injuries [3–6]. Studies have found that LIPUS can not only exert non-invasive physical stimulation through low-intensity delivery in the mode of pulsed waves but also can carry out biological therapy, which helps to mitigate inflammation, facilitate tissue repair, inhibit edema formation, and stimulate angiogenesis [7]. At present, therapeutic LIPUS has been experimentally or clinically studied in many diseases and achieved good efficacy [8–11].

Overactivated inflammatory response and abnormal immunologic state in patients with viral pneumonia were significantly associated with a high risk of severe cases [12, 13]. Given that LIPUS can up-regulate the expression of anti-inflammatory genes, upregulate immunosuppressive cell regulators and anti-inflammatory cytokines [14], and play a good role in mitigating inflammation, we tried to use wearable LIPUS to irradiate lung inflammation to improve clinical symptoms and shorten the disease course. At the same time, the physical effect of LIPUS can promote the loosening of the sputum scab attached to the inner wall of the small bronchi through low-frequency impact force [15, 16] and promote the discharge of sputum in the small airway. The mechanical and cavitation effect of ultrasound can also destroy the thrombus surface, expose the thrombolytic site, and promote the combination of thrombolytic drugs with fibrin to promote thrombolysis [17], thereby improving pulmonary blood circulation and preventing venous stasis.

Therefore, we propose a strategy of LIPUS treatment program for patients with viral pneumonia. We aim to conduct a randomized double-blind controlled clinical superiority trial that could evaluate the efficacy of LIPUS on hospitalized patients with viral pneumonia.

### Objectives {7}

#### Primary objective

The primary objective is to examine whether LIPUS therapy is more effective to mitigate lung inflammation in viral pneumonia patients than conventional symptomatic care control.

#### Secondary objectives

To determine whether there is a difference in pulmonary function between LIPUS treatment group and control groupTo determine whether there is a difference in arterial oxygen saturation and serum inflammatory factor levels between LIPUS treatment group and control groupTo determine whether there is a difference in the improvement of clinical symptoms among patients

### Trial design {8}

The study design is a randomized, double-blind, controlled clinical superiority trial. Participants will be randomized into three groups in a 1:1:1 allocation ratio: (1) the intervention group (LIPUS stimulus), (2) the control group (null stimulus), or (3) the self-control group (stimulated vs non-stimulated areas). Treatment is expected to last 7 days, and participant recruitment and data collection will be completed within 12 months. The study protocol flow chart is described in Fig. 1.

**Fig. 1 Fig1:**
[figure not shown]
Participant flow chart. LIPUS, low-intensity pulsed ultrasound

## Methods: participants, interventions, and outcomes

### Study setting {9}

This is a single-center clinical study, which will be carried out in the Lingang Campus of Shanghai Sixth People’s Hospital Affiliated to Shanghai Jiao Tong University School of Medicine.

### Eligibility criteria {10}

Eligible participants will undergo laboratory and imaging examinations to confirm the diagnosis of viral pneumonia and to assess eligibility to participate in the study.

Patients who meet all the following enrollment criteria will enter this study after signing the informed consent: (1) age 18–80 years old; (2) hospitalized patients had pneumonia-related symptoms, computed tomography (CT) examination met the diagnostic criteria of pneumonia, and the etiology examination suggested a viral origin; (3) patients who can cooperate with various examinations during clinical research; (4) the patient participates voluntarily, and he/she or his/her family agrees and signs the informed consent.

Patients who meet the following criteria will be excluded: (1) other types of pneumonia, such as bacterial pneumonia, mycoplasma pneumonia, falling accumulation pneumonia, etc.; (2) patients with bronchiectasis or lung malignancies; (3) patients with chest skin injury who cannot wear the LIPUS device; (4) pregnant and breastfeeding women; (5) contraindications to the therapeutic ultrasonography (US), including dermatological conditions, local abnormal sensations in the chest or back, epilepsy, etc.; (6) patients with mental illness or unable to communicate normally with staff.

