## Outcomes {12}

### Primary outcome

The primary outcome measure will be the difference in the extent of absorption and dissipation of lung inflammation on CT images. Result comparisons will be made between the test group and the control group and between the LIPUS-treated and non-treated areas within the self-control group.

Pulmonary inflammation on CT images will be assessed by an expert chest radiologist before and 7 days after treatment to compare the area and volume of inflammation in the target area of the lung, as well as the area absorption rate (AAR) or volume absorption rate (VAR). A Pair software will be used to mark and 3D reconstruct the target area of CT images and record the data of pulmonary inflammation changes. AAR is defined as [(target site inflammation area before treatment − target site inflammation area after treatment)/target site inflammation area before treatment] × 100 (%). VAR is defined as [(target site inflammation volume before treatment − target site inflammation volume after treatment)/target site inflammation volume before treatment] × 100 (%).

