#### The course of pneumonia

The hospitalization time and the time from the first symptom to discharge of the patients in each group will be counted. The discharge criteria for confirmed patients are as follows: (1) body temperature returned to normal for more than 3 days, (2) respiratory symptoms improved significantly, (3) pulmonary imaging showed significant improvement in acute exudative lesions, and (4) two consecutive viral antigen or nucleic acid tests were negative.

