### Recruitment {15}

Participants will be recruited from the Lingang Campus of Shanghai Sixth People’s Hospital Affiliated to Shanghai Jiaotong University School of Medicine, and they are all inpatients who have undergone laboratory and imaging examinations to confirm the diagnosis of viral pneumonia. The doctors will contact with the patients and their families, and after obtaining the informed consent from the patients themselves or their family members, doctors will conduct screening according to the inclusion and exclusion criteria. Only those who meet all recruitment requirements and do not meet any exclusion criteria will participate in this study.

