## Assignment of interventions: allocation

### Sequence generation {16a} and concealment mechanism {16b}

Participants will be randomized into three groups (LIPUS group; control group; self-control group) in a ratio of 1:1:1 using a computer-generated randomization sequence. Research assistants not involved in clinical care or outcome assessment will prepare sequentially numbered, opaque, sealed envelopes based on the randomization list and ensure the confidentiality and independence of the allocation data. When appropriate, the assistant will open envelopes and ensure the coordination of therapeutic interventions.

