## Strengths and limitations

We proposed and demonstrated a novel approach to promote inflammatory uptake in viral pneumonia. Given that the current clinical recovery mainly depends on the body’s self-limiting and conventional symptomatic treatment, LIPUS, as a new therapy method, might be a major advance in the treatment of viral pneumonia. The clinical application of wearable and easily operative LIPUS without radiation and side effects may be more extensive than limited to viral pneumonia. Combined with the therapeutic mechanism, it is speculated that LIPUS may also play a certain role in the treatment of other types of pneumonia. And it should also have advantages in pediatric patients and home treatment.

This study has two main limitations. First, we only compared the difference between LIPUS treatment and non-treatment and did not compare LIPUS with commonly used clinical anti-inflammatory drugs, immunomodulatory drugs, or anticoagulation, which made the observation of clinical efficacy not comprehensive enough. Second, this is a single-center study. Due to the limited number of wearable US devices, it has not been further developed in other research centers.

To the best of our knowledge, this study is the first clinical study of the efficacy of therapeutic LIPUS in the treatment of viral pneumonia. Compared with drug treatment or other artificial/mechanical assisted treatment equipment, a wearable LIPUS device will be simpler, safer, and more comprehensive and is expected to greatly improve the continuity and compliance of clinical treatment for patients with viral pneumonia.

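### The LIPUS-versus-control CT comparison takes no account of illness day in a largely self-limiting disease: precision is lost and chance imbalance goes unadjusted, but there is no bias

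*Protocol article*

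**What the plan says.** All references are to the protocol article.

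- **Entry.** Eligibility criteria {10} asks that "hospitalized patients had pneumonia-related symptoms, computed tomography (CT) examination met the diagnostic criteria of pneumonia, and the etiology examination suggested a viral origin". None of the four inclusion or six exclusion criteria concerns time since onset. Recruitment {15} treats the list as complete: "Only those who meet all recruitment requirements and do not meet any exclusion criteria will participate in this study".
- **Natural course.** Strengths and limitations says that "clinical recovery mainly depends on the body", through its "self-limiting and conventional symptomatic treatment". The Abstract says the same.
- **Outcome.** Under Primary outcome, lung inflammation on CT "will be assessed by an expert chest radiologist before and 7 days after treatment". It is expressed as area or volume absorbed, in percent of the baseline value. The clock starts at treatment, not at onset.
- **Allocation.** Sequence generation {16a} describes assignment "in a ratio of 1:1:1 using a computer-generated randomization sequence". It names no stratification factor, and does not say that there is none.
- **Analysis.** Statistical methods {20a} compares groups with an independent two-sample test, names no covariate, and only describes baseline characteristics.
- **Onset date.** The course of pneumonia counts "the time from the first symptom to discharge", which cannot be computed without the date of first symptom.

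**The concern.** If viral pneumonia largely resolves by itself, the amount absorbed in a 7-day window depends partly on where that window falls in the illness. One patient may start while exudate is still forming and another while it is clearing. Dividing by baseline extent does not remove this, because two lesions of equal volume can be heading in opposite directions.

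In the LIPUS-versus-control comparison, which serves the primary objective, this variation goes into the error term, and any chance difference between the arms in illness day goes into the estimate. In arms this small such differences are not rare. The self-control contrast is not exposed, since both lung areas belong to the same patient on the same day. At stake are the precision and the interpretability of the between-arm result. The data needed to improve both are already being obtained.

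**Working it through.** **1. The plan's own figures.** Sample size {14} gives 66 participants at 1:1:1, so 66/3 = 22 per arm, raised for 5% dropout to 66/0.95 = 69.5, that is 70. This step reproduces. The 66 itself cannot be reproduced: it is tied to feasibility, and no effect size or SD is stated. Solving backwards for 90% power at two-sided 0.05, the detectable standardised difference is (1.960 + 1.282) × √(2/22) = 0.98.

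**2. Chance imbalance.** The SD of the between-arm difference in mean illness day is SD × √(2/22) = 0.302 × SD. The SD of illness day is not in the documents, so a range is assumed.

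| Assumed SD (days) | SD of difference (days) | Chance of more than 1 day's imbalance |
|---|---|---|
| 2 | 0.60 | 10% |
| 3 | 0.90 | 27% |
| 4 | 1.21 | 41% |

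**3. Effect on the estimate.** Let R² be the share of variance in absorption explained by illness day (assumed). The 95% range of the chance shift in the LIPUS-control difference is ±1.96 × √R² × √(2/22): ±0.19, ±0.26 and ±0.32 outcome SD for R² = 0.1, 0.2 and 0.3.

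**4. Type I error.** In 40,000 simulated trials under no effect, the unadjusted test rejected in 5.1% (R² 0.2) and 5.3% (R² 0.5). In the roughly 10% of trials where imbalance exceeded half an SD of illness day, it rejected in about 12% and 25%. The overall rate holds; the rate given a visible imbalance does not.

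**5. Gain from adjustment.** The equivalent sample size is 1/(1 − R²): 1.11 at R² = 0.1 and 1.43 at R² = 0.3. For the 44 patients in the two arms, that is 44/0.9 = 49 or 44/0.7 = 63. Power is Φ(d × √(22/2)/√(1 − R²) − 1.96). At an illustrative d = 0.8:

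| R² | Power |
|---|---|
| 0 (unadjusted) | 75.6% |
| 0.1 | 79.9% |
| 0.2 | 84.3% |
| 0.3 | 88.7% |

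These are normal approximations. Simulated analysis of covariance at R² = 0.2 gave 80.9%, somewhat lower.

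**6. Cost of the extra terms.** With k covariate terms and N = 44, variance rises by about 1 + k/(N − k − 3): 1 + 1/40 = 1.025 for one term and 1 + 2/39 = 1.051 for two. The net gain is then 1.11/1.025 = 1.08 (one term) or 1.11/1.051 = 1.06 (two terms) at R² = 0.1, and 1.43/1.025 = 1.39 or 1.43/1.051 = 1.36 at R² = 0.3. Adjustment pays for itself once R² exceeds 1 − 1/1.025 = 2.4% or 1 − 1/1.051 = 4.9%.

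**The case against.** The sponsor could fairly reply that broad entry with a randomised control is valid, that chance imbalance is what the 0.05 level already allows for, and that age, virus or comorbidity could be singled out in the same way. The first two points stand: this is a matter of precision, not validity. The third is weaker, because the article itself names the self-limiting course as a main source of recovery, and the onset date is already obtained.

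The design also has a self-control arm, added to deal with differences between patients, and the Discussion foresees that a LIPUS-control difference might reflect such differences. But that arm protects only its own within-patient contrast.

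Covariates may also be specified in a fuller document not shown. That is possible, but Statistical methods {20a} does name a test, and the test is unadjusted.

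A reader might infer more than the documents support:

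- **That the result is biased or alpha inflated.** It is not (step 4).
- **That allocation is unstratified.** The article is silent on this, and a condensed article may omit it.
- **That patients enter on any day whatever.** They must be hospitalised, symptomatic and CT-positive. Plans to promote participant retention {18b} also drops the data of those who do not complete 7 days of treatment, so the spread may be narrower than the larger SDs assumed here.
- **That the envelopes should be restratified.** Strata without blocking within them balance nothing, and Trial status schedules recruitment from October 2022.
- **That a single straight line in illness day recovers the whole gain.** A course that worsens and then clears need not be linear, and may differ by virus.

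**Conclusion.** The point holds as one of efficiency and interpretability. The stated between-arm analysis leaves out a plausible and probably important baseline predictor whose raw date is already obtained. The LIPUS-versus-control comparison remains unbiased, with type I error near 5%.

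Only the 22 per arm comes from the documents. If illness day explained 10-30% of outcome variance, adjustment would be worth about 11-43% more patients before the cost of the extra terms, and about 6-39% after it. Grouping the covariate and imprecise recall would lower this further. If illness day explained less than about 2-5%, there would be no gain. The self-control comparison is unaffected.

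**What to change.** Replace the unadjusted LIPUS-versus-control test of CT absorption with a prespecified linear model (analysis of covariance) containing treatment arm and days from first symptom to first treatment. Fix the form of the covariate in advance and let it be non-linear, for example two or three categories. Set the cut-points without reference to outcomes, and state how an unknown onset date is handled.

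Date the change before the groups are revealed. Because Procedure for unblinding {17b} reveals them only once the primary and secondary analyses are complete, this should in practice mean before any comparison is run. The envelopes are opened just before the first treatment session, so the covariate is in effect fixed at baseline.

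The cost is small: no new data, one or two of the 42 residual degrees of freedom, and reliance on patients' recall of onset, which weakens the gain without invalidating the adjustment. Eligibility and allocation stay unchanged.

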### Who will take informed consent? {26a}

The research assistant ([name]) will take informed consent before trial baseline evaluation in the participant reception room. Caregivers will give informed consent to potential participants before the time point of allocation. Participants will be notified why the study is conducted, what they will be doing, and the possible benefits and risks. If participants have any questions, they are free to ask them, and they can decide whether to participate in the study after fully understanding.

### Additional consent provisions for collection and use of participant data and biological specimens {26b}

No additional biological samples were collected for the study. No subject data are currently available for future studies. Additional consent from participants will be obtained if relevant data from participants is required in future studies.

## Interventions

### Explanation for the choice of comparators {6b}

The usual practice combined with empty stimulation (a placebo effect) was selected as the comparator condition in order to detect whether the anticipated benefit of LIPUS treatment would produce better anti-inflammatory effect than the current conventional symptomatic care. In addition, a self-control group (LIPUS stimulated areas versus non-stimulated areas) was established to eliminate the interference of individual differences on the results.

### Intervention description {11a}

All participants will participate in a health education of approximately 20 min led by the research assistant prior to intervention treatment. The content of the education includes the transmission route of viruses, preventive measures, clinical manifestations, general treatment measures, etc. It is recommended that patients maintain hygiene, exercise moderately, drink an appropriate amount of water, and have a light diet.

Participants in the intervention group will be treated with wearable LIPUS therapeutic apparatus (UT – HP 05 21, Shanghai, China) for 7 days at a frequency of 572 kHz, an intensity of 820 mW/cm^2^, and a duty cycle of 50% (1 s inter-stimulus interval). The apparatus consists of two movable ultrasound probes and a central device. The operator fixed the ultrasound probes on the patient’s chest or back and adjusted the position of the probes according to the shape and scope of the lung lesion to perform vertical or parallel sonication therapy (Supplementary Fig. 1). During hospitalization, patients received 30-min treatments at 8:00 am and 2:00 pm daily.

Participants in the control group will be given a “null stimulus,” that is, the LIPUS therapeutic apparatus will be worn but the sonication treatment will not be started. These patients will be treated at the same time of day as the patients in the test group, but neither the patients nor the operators of the LIPUS equipment are aware of the grouping.

Participants in the self-control group will be compared the LIPUS-treated area with the non-treated area in the lungs. First, a CT examination is performed to locate the body surface of the inflammatory exudative area. If the patient has bilateral pulmonary exudative inflammation, LIPUS treatment will be performed on one side of the lung, and the other will serve as the self-control group. Limited by the frequency of LIPUS, ultrasound cannot penetrate through one lung tissue to the other, and its maximum penetration depth is limited to the inside of the target lung. If the patient has unilateral pulmonary exudative inflammation, the inflammatory area will be divided into the upper and lower areas, and a single-area stimulus will be performed. The diameter of the two ultrasound probes is approximately equal to the width of the intercostal space, and the probes can be placed in the same intercostal space or in different intercostal spaces. The direction of sound beam can be adjusted manually. Limited by the width of the sound beam and the plane of sonication, the non-target inflammatory area above or below can be considered not to be affected.

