### Criteria for discontinuing or modifying allocated interventions {11b}

Patients are free to withdraw from participation in the study at any time upon request, without any consequence. If a participant chooses to discontinue the study intervention, we will not collect or use their data.

LIPUS is an FDA-approved and safe treatment modality. To date, no adverse events have been reported with the low-power LIPUS regimen in soft tissue. Therefore, we anticipate that the risk to the safety of participants will be minimal. However, nursing staff will still monitor potential mild adverse reactions such as mild local swelling, spotting bleeding, enhanced local pain response, and local hyperesthesia or decrease. In case of corresponding symptoms, appropriate symptomatic treatment shall be carried out. Regardless, participants can withdraw from the study at any time if they experience adverse events that are unacceptable to them.

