## Assignment of interventions: blinding

### Who will be blinded {17a}

Both patients and clinic staffs (caregivers, outcome assessors, and statistical analysts, etc.) will remain blind to group allocation. Whether the intervention is LIPUS-treated or non-stimulated will not be revealed throughout the study.

The clinician ([name]) who performed LIPUS therapy was not blinded to the grouping results and the course of treatment. The clinicians, [name] and [name], have access to the final trial dataset.

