## Trial status

The first version of the protocol was approved by the institutional ethical committee on June 6, 2022, and this protocol is version 1.0. The design and improvement of the chest wearable LIPUS therapeutic device, as well as the confirmation of ultrasonic stimulation parameters, are currently underway. Patient recruitment and data collection will be carried out in our hospital from October 2022 to October 2023, and data will be collated and analyzed later.

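### The null stimulus is a worn device that is never started, and nothing described makes it indistinguishable from an active session, so the claimed patient blind is asserted but not supported

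*Protocol article*

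**What the plan says.** Trial design {8} calls the study double-blind. Explanation for the choice of comparators {6b} gives the control arm's purpose: "The usual practice combined with empty stimulation (a placebo effect) was selected as the comparator condition". Intervention description {11a} then defines that stimulus: "the LIPUS therapeutic apparatus will be worn but the sonication treatment will not be started". Control sessions take place at the same times of day as active ones, and the same section says that neither patients nor operators know the grouping.

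The active device is used "for 7 days at a frequency of 572 kHz, an intensity of 820 mW/cm^2", pulsed at a 50% duty cycle with a 1 s interval. On timing, "patients received 30-min treatments at 8:00 am and 2:00 pm daily".

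Who will be blinded {17a} states: "Both patients and clinic staffs (caregivers, outcome assessors, and statistical analysts, etc.) will remain blind to group allocation". It goes on to say that the clinician who gave the LIPUS therapy was not blinded. Implementation {16c} has the allocation code passed to the LIPUS experimenter.

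Criteria for discontinuing or modifying allocated interventions {11b} lists potential mild reactions to be monitored, including "enhanced local pain response, and local hyperesthesia or decrease". Trial status reports on the device: "The design and improvement of the chest wearable LIPUS therapeutic device, as well as the confirmation of ultrasonic stimulation parameters, are currently underway".

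**The concern.** A sham protects the patient blind only if the patient, and the staff around the patient, cannot tell it from the active treatment. Here the sham is made by leaving out the start of sonication. The article mentions no simulated run, no matched display and no check of whether the blind held. Two claims therefore rest on something the text does not supply: that patients are blind, and that the control arm carries the same placebo effect as the LIPUS arm.

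Several secondary outcomes depend on effort or judgement: the spirometry measures, the volume of sputum coughed up, rales on auscultation, and discharge, which rests partly on improvement in respiratory symptoms. If control patients or ward staff recognised the null condition, these outcomes could favour LIPUS through expectation alone.

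Two indirect routes could also matter. Non-protocol treatments are only discouraged and are reported by the patient ({11d}), so knowledge of the arm could make their use unequal. Data from patients who stop or withdraw are not kept ({11b}, {18b}, {19}), so controls who lost confidence in the device and left would drop out of the comparison.

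**Working it through.** The article states no figure on this point, so there is none to reproduce. The check is a count of sessions followed by a comparison of sections.

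**Exposure.** The inputs come from {11a}: 2 sessions per day, 7 days, 30 minutes each.

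- Sessions: 2 x 7 = 14.
- Time wearing the device: 14 x 30 min = 420 min = 7 h per patient.

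This is the opportunity for any cue to be noticed. It does not show that a cue exists.

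**What each section implies for the blind.**

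| Section | What it says | Consequence |
|---|---|---|
| {6b} | Empty stimulation is chosen to carry a placebo effect | Control sessions need to be credible as treatment |
| {11a} | Null device is worn, sonication not started | No simulated run is described |
| {11a} | Patients and operators are unaware of grouping | Cannot hold for the person who must start the device in one arm and not in the other |
| {16c} | Code is given to the LIPUS experimenter | Operator knows the arm |
| {17a} | Treating clinician not blinded; patients, caregivers and assessors blind | Contradicts {11a} on operators; patient blind restated without a mechanism |

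A device with a built-in sham setting would let the operator press start in both arms and stay blind. Passing the code to the operator fits a sham made simply by not starting.

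**Is the difference perceptible?** The article does not say whether active sonication can be felt or heard, or whether a running state shows on the apparatus. If neither is perceptible, an unstarted device could be an adequate sham. If either is, it would not be. The text does not settle which case applies.

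**Size of bias.** Suppose a fraction q of control patients recognise the null condition, and recognition shifts an effort-dependent outcome by e standard deviations. The bias is then about q x e. The documents give neither quantity. With q anywhere from 0 to 1, the bias ranges from 0 to e, and e itself is unknown. Any single number would be an assumption and not a finding about this trial.

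**Where it could act.** The primary outcome is CT area or volume absorption, read by a radiologist, with outcome assessors stated to be blind. One of its two comparisons is within patients, between treated and untreated areas, so unequal expectation between arms does not enter it. The exposed outcomes are the secondary ones named above. CT could be reached only indirectly, through non-protocol treatment or selective withdrawal.

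**The case against.** The strongest reply is that perceptibility is not documented. A reader might infer that control patients can tell they are untreated, but no section says so. The apparatus is described only as two probes and a central device. An unstarted treatment need not mean a dark or unpowered unit, and patients in parallel arms never experience the other condition. This stands, and it is why the point is that the blind is unsupported, not that it is broken.

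Other tempting steps also fail:

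- The local sensations in {11b} are potential reactions to be monitored, listed just after a statement that no adverse events have been reported with the low-power regimen in soft tissue. They are not expected sensations, and nothing says that only an active device could cause them.
- The exclusion for abnormal chest or back sensation is listed as a contraindication to therapeutic ultrasound. It is not evidence that treatment is felt.
- Nothing shows that patients compare devices with one another.
- The post-treatment check for rales comes 2 h after the daily treatment, so it does not put the physician beside a running or idle unit.
- The output figures in {11a} say nothing about whether a patient can detect it.
- Discharge also requires normal temperature, improved imaging and two negative viral tests, which limits the weight of the symptom criterion.

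It can also be said that a condensed article leaves sham detail to the full protocol. That has less force here. The article does not stay silent on the sham but defines it, and the definition does not support the blinding claims made beside it. The contradiction about operators is in the text whatever the full protocol says.

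**Conclusion.** The point holds in limited form. The control condition as defined does not support the patient blind claimed in {11a} and {17a} or the placebo match intended in {6b}. The statement in {11a} that operators are unaware conflicts with {16c} and {17a}, and with the act of leaving the device unstarted.

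The size of any bias is unknown, because the article does not say whether sonication or a running state can be perceived. If it can, the bias would fall mainly on the effort- and judgement-based secondary outcomes, possibly also on withdrawal and non-protocol treatment, and not directly on the CT reading. The last part of that judgement assumes that the CT reader is blind, as stated. The point merits correction because the trial's double-blind label depends on it, but it does not by itself undermine the primary comparison.

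**What to change.** In Intervention description {11a}, replace the unstarted device with a sham mode: the same apparatus, started and run for the same 30 minutes with the same display and procedure, but with acoustic output disabled inside the unit. If the operator can then start both kinds of session without the code, revise {16c} and {17a} to say so. Otherwise correct the statement about operators in {11a}. Ask patients and outcome assessors to guess the group at day 7, and report the guesses by arm.

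If a sham mode is not feasible, withdraw the claim that patients are blind from {11a} and {17a}, and label spirometry, sputum, rales and symptom-based discharge as open to expectation bias. If active output is known to be imperceptible and the running state is hidden, stating this in {11a} would largely meet the concern about patients.

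The cost is one device setting, on equipment whose design Trial status describes as still in progress, and one added question. The downside is small: any sensation from active output could not be fully mimicked, although the group guess may help to show whether that matters.
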